## Methods/Design

### Study design

The Girls on the Move intervention is a group randomized trial involving 24 racially diverse, urban schools in low SES areas in the Midwestern U.S. In years 2, 3, and 4 of the 5-year study (2011–2016), 8 schools will be randomly assigned to either receive the intervention (n = 4/year) or serve as the control condition (n = 4/year). The research will be reported in accordance with Consolidated Standards of Reporting Trials (CONSORT) recommendations [24].

In order for their school to be included in the study, school administrators must be willing to accept the randomization status of the school and sign a memorandum of understanding. Schools will be included in the study based on the following criteria: (1) location in urban community setting; (2) enrollment greater than 100 girls in each school or more than double the number of girls needed for the study site (n = 50 per school) in any combination of 5^th^, 6^th^, 7^th^, and/or 8th-grade; and (3) student body comprised of at least 50% minority versus non-minority race or ethnicity and including a similar percentage enrolled in the free and reduced lunch program. Schools were excluded if administrators were not interested in participating, did not agree to random assignment, or could not guarantee their availability at 9-month post-intervention F/U.

To avoid any bias, schools are paired prior to randomization based on the following criteria: school type (e.g., academic grades offered), school size, percentage of students who are white vs. non-white race, and proportion of students receiving the free and reduced lunch. Prior to the start of the school year, the PI and project manager inform each principal regarding the randomization status of his or her respective school to assist each principal with future planning. Principals are told that the randomization information must remain confidential until completion of baseline data collection in the fall.

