### Sample size determination and data analysis

#### Power calculations

Sample size calculations incorporated school-based research power approaches [65,66] and were informed by the work done in our pilot study and other studies using MVPA as a primary outcome [67,68]. We assumed a small effect size of 0.20 and an intraclass correlation coefficient (ICC) of 0.02, as noted from the Trial for Activity in Adolescent Girls [67]. Assuming a standard deviation of 80 for minutes of MVPA over 7 days [68], this effect size of 0.20 corresponds to a difference of 16 minutes/week between groups. Given that girls receiving the intervention are encouraged to accumulate at least 60 minutes/day of MVPA, this mean difference is reasonable to expect with a control group that consists of a number of girls who may have never been involved in any organized MVPA due to obstacles, such as limited free or low-cost programs [69]. Using this effect size and ICC, 24 schools (12 intervention) with 50 girls per school would provide power .80 and alpha = 0.05 for two-tailed comparison between two groups. To allow for 20% attrition (12 girls per school) [36,69-71], we plan to recruit 62 girls per school each year.

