#### Data analysis

Data will be analyzed using SAS 9.3 (SAS Institute Inc., Cary, NC) [72]. Outcome measures include the primary outcome: minutes of MVPA; secondary outcomes: CV fitness, BMI, and percent body fat; and mediating cognitive and affective variables. Potential covariates measured at baseline are personal factors and behaviors. To adjust for non-independence of observations within each school and the dependence within person, analyses below will be carried out using a multilevel model approach frequently used in group randomized trials [73] that will incorporate baseline measures as covariates [74,75]. Multilevel generalized linear models [73,76] will be fit for ordinal, and discrete outcomes using appropriate link functions. Assumptions of normality for continuous outcome variables will be evaluated; normalizing transformations or generalized linear mixed effect models will be used if warranted [76].

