#### Preliminary analyses

Descriptive statistics, such as means and proportions, will be provided for outcomes and baseline measures. Pattern of missing data will be evaluated and missing at random mechanism will be assumed [77]. We will collect information on participants who dropped out and baseline characteristics of those who dropped out will be compared by group to provide information of any potential attrition bias.

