#### Primary analyses

Primary analysis is of intention to treat type [78,79], which gives a conservative estimate of treatment effect compared with what would be expected if there was full compliance [80]. Effect sizes and their confidence intervals (adjusted for baseline values of outcomes and nested study design) will be computed. Variance components (school and participants) will be estimated.

We will use: Statistical Model #1: Outcome (after 17 weeks) = outcome (baseline) + study group + covariates. The essential parameter tested in this model is the coefficient for the study group variable. Covariates will be included if preliminary analyses reveal group differences at baseline despite randomization. We will model 9-month post-intervention F/U MVPA, controlling for MVPA after 17 weeks (immediately post-intervention): MVPA (9-month post-intervention F/U) = MVPA (after 17 weeks) + study group + covariates.

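### Additional covariates enter the primary model only when the arms differ at baseline, which selects on imbalance rather than on relation to MVPA and leaves those terms open until baseline data by arm have been seen

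*Protocol article*

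**What the plan says.** Under Primary analyses, the protocol article writes Statistical Model #1 as "Outcome (after 17 weeks) = outcome (baseline) + study group + covariates" and adds: "The essential parameter tested in this model is the coefficient for the study group variable". What fills the last term is decided by this rule: "Covariates will be included if preliminary analyses reveal group differences at baseline despite randomization".

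The pool is described under Data analysis: "Potential covariates measured at baseline are personal factors and behaviors". The section Personal factors and behaviors lists what is collected: PE days, sport or lessons, screen and phone time, lunch-programme status, age, grade, race, ethnicity and pubertal stage. Nothing in the article picks covariates from that pool, gives a prognostic criterion, or says what counts as a difference.

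The same covariate term appears in the 9-month MVPA model and in Models #1a, #1b and #2 for mediation.

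**The concern.** Adjusting for a baseline variable gains precision to the extent that the variable predicts the outcome. How far the arms differ on it is a separate matter. A rule keyed to observed differences therefore omits a strong predictor that happens to be balanced and admits a weak one that happens not to be.

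The rule also means that the model behind the tested coefficient is not fully known until someone has compared the arms at baseline. With no test, threshold or list, two careful analysts could follow the sentence and arrive at different primary models. At stake are precision that the trial could have had from data it already collects, and an avoidable challenge to the choice of model once the result is known.

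This is a rule that the article states, not a detail left to a separate analysis plan.

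**Working it through.** **Starting point.** The article gives no figure for the covariate rule. The nearest is its power of 0.80, from 24 schools (12 per arm), 50 girls per school, two-sided alpha 0.05 and "We assumed a small effect size of 0.20 and an intraclass correlation coefficient (ICC) of 0.02".
- Design effect = 1 + 49 × 0.02 = 1.98.
- Noncentrality = 0.20 / √(2 × 1.98 / 600) = 2.46.
- Power = 0.69 by the normal approximation, or 0.65 by the t distribution with 22 df.

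The stated 0.80 is not reproduced from these inputs. That is a separate matter on which this point does not depend, but 0.65 is the baseline for the comparison of power below.

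**How often the rule would act by chance.** Assume K independent candidates, each tested at 5%. The article gives neither K nor a level. The chance of at least one flag is 1 − 0.95^K:

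| K | Chance of at least one flag |
|---|---|
| 5 | 0.23 |
| 8 | 0.34 |
| 10 | 0.40 |
| 12 | 0.46 |

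Age, grade and pubertal stage are plainly related, so these are upper figures. For K = 10, a common correlation between the tests of 0.2 to 0.4 (assumed) gives about 0.37 to 0.32.

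**What the rule recovers.** This is a school-level simulation with 12 schools per arm, 50 girls per school and effect 0.20. It assumes 8 covariates with covariate ICC 0.05, each with the same correlation with the outcome after baseline adjustment. Baseline tests are at school level at 5%; there were 8,000 runs.

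| Correlation | No extra covariates | Imbalance rule | Fixed set |
|---|---|---|---|
| 0.1, power | 0.625 | 0.627 | 0.687 |
| 0.2, power | 0.565 | 0.572 | 0.816 |
| 0.1, type I error | 0.048 | 0.047 | 0.052 |
| 0.2, type I error | 0.050 | 0.038 | 0.052 |

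The rule gains almost none of the available precision. Type I error under it is at or below the nominal 5%.

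**Limits of the simulation.** Slopes are treated as known and pairing is ignored. The covariates also raise the outcome ICC above the protocol's 0.02: 0.08 × 0.05 + 0.92 × 0.02 = 0.022 at correlation 0.1, and 0.32 × 0.05 + 0.68 × 0.02 = 0.030 at 0.2. Part of the gap is therefore that extra between-school variance.

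**Cross-check with the ICC held at 0.02.** Let the covariates explain a share R² of the variance equally at school and girl level, so noncentrality = 0.20 / √(2 × 1.98 × (1 − R²) / 600), with 22 df.
- R² = 0: 2.46, power 0.65.
- R² = 8 × 0.1² = 0.08: 2.57, power 0.69.
- R² = 8 × 0.2² = 0.32: 2.99, power 0.81.

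On this basis a fixed set gains about 4 to 16 percentage points. The upper end needs covariates that explain a third of the variance left after baseline MVPA, which is generous.

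**The case against.** Several arguments on the other side have force.

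- **The core of the model is fixed.** Model #1 always contains the baseline outcome and study group, and the article commits to a multilevel approach "that will incorporate baseline measures as covariates". Baseline MVPA is plausibly the strongest predictor. This stands, and it confines the point to the additional terms. To say that the primary model as a whole is unfixed would go too far.
- **Error rate.** A reader might infer that a pre-test of this kind inflates false positives. The simulation does not support that: the rule is mildly conservative.
- **Clustering.** A reader might infer that girl-level tests would flag school-clustered factors far more often than 5%. If tests ignored schools, the formula 2 × (1 − Φ(1.96/√(1 + 49 × ICC))) would give 16%, 29% and 42% per variable at assumed ICCs of 0.02, 0.05 and 0.10. But the article specifies no such test. Its Data analysis section says that the analyses that follow account for schools, and under Study design "schools are paired prior to randomization based on the following criteria: school type (e.g., academic grades offered), school size", together with racial mix and lunch-programme share. Those rates should not be attributed to this plan.
- **Not every difference need be chance.** Principals learn the allocation before the school year, and girls are then recruited first come, first served. Differential enrolment is possible despite the request for confidentiality, so looking at baseline balance is not meaningless. That supports a descriptive baseline table; it does not make imbalance a good selector. A fixed set adjusts for its listed variables whether a difference arose by chance or through recruitment.

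Nor is there a defect in the baseline summaries themselves ("Descriptive statistics, such as means and proportions, will be provided for outcomes and baseline measures"). The weakness lies only in letting them choose the model.

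**Conclusion.** The point holds in a limited form. The protocol states a data-dependent rule for the additional covariates of its primary model, and the 9-month and mediation models carry the same term. The rule selects on imbalance, which does not identify predictors of MVPA. The consequences are lost precision and analyst latitude.

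The size can only be illustrated. A chance flag somewhere among the candidates has probability 23% to 46% for 5 to 12 independent candidates tested at 5%, and less if they are correlated. The precision forgone depends on how well the covariates predict MVPA beyond baseline MVPA, which the article does not say. The number of candidates, test level, covariate ICC and correlations are all assumptions. The case against the rule does not need them: it follows from the selection criterion itself.

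**What to change.** Delete the sentence that makes inclusion depend on baseline group differences. In its place, name a short list of expected predictors already collected, for example grade or age, pubertal stage, race/ethnicity and lunch-programme status. Include them with the baseline outcome whatever the observed balance. Apply the list to the covariate term of the 9-month and mediation models as well. Keep baseline comparisons descriptive, and put any adjustment prompted by imbalance in a sensitivity analysis.

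The cost is one sentence and a few girl-level degrees of freedom among about 1,200 girls (24 × 50). No new data are needed.

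Fixed effects for the matched pairs are not part of this change. Twelve pairs would use 11 of the 22 school-level degrees of freedom; on the protocol's own inputs power would fall from 0.65 to 0.61 unless pairing removed enough between-school variance to make up for it. That is a separate trade-off.

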### Aims and hypotheses

The main study aim is to evaluate the efficacy of our comprehensive 17-week school-based intervention in increasing girls’ minutes of MVPA and improving CV fitness, BMI, and percent body fat immediately post-intervention (after 17 weeks) and at 9-month post-intervention follow-up (F/U; 9 months after end of intervention). The primary outcome is minutes of MVPA measured after 17 weeks. The intervention includes three components, two of which are individual-level: 1) two face-to-face motivational, individually tailored counseling sessions with a registered nurse, and 2) an interactive Internet-based session during which each girl receives individually tailored motivational and feedback messages (11 weeks). One group-level component, a PA club led by PA instructors (e.g., individuals from community who have experience conducting youth physical activity programs; teachers, including physical education; and sports team coaches), provides an important venue after school to assist girls in establishing a behavioral pattern of MVPA. Girls receiving the intervention will be compared to those in control schools having usual school offerings, some of which may include physical education.

Specific hypotheses include:

•Immediately post-intervention, minutes of MVPA (measured by accelerometer) will be greater by 16 minutes/week among girls in intervention, as compared to control, schools.

•At 9-month post-intervention F/U, minutes of MVPA will be greater among girls in the intervention than control schools.

•Immediately post-intervention and at 9-month post-intervention F/U, CV fitness will be higher and BMI and percent body fat will be significantly lower among girls in the intervention than control schools.

A secondary objective is to examine if MVPA changes are mediated by cognitive (e.g., perceived benefits of PA, barriers to PA, PA self-efficacy, social support) and affective variables (e.g., enjoyment of and motivation for PA).

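### The only 9-month model adjusts for 17-week MVPA, which the intervention is meant to raise, so its group coefficient is not the 9-month difference the trial hypothesises.

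*Protocol article*

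**What the plan says.** The main aim in the protocol article covers efficacy both at 17 weeks and 9 months after the intervention ends. Under Aims and hypotheses, the 9-month hypothesis reads "At 9-month post-intervention F/U, minutes of MVPA will be greater among girls in the intervention than control schools". This is a plain difference between the arms at that time.

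The same section says "The primary outcome is minutes of MVPA measured after 17 weeks" and expects that this outcome "will be greater by 16 minutes/week among girls in intervention, as compared to control, schools".

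Primary analyses then gives two models. The 17-week model is "Outcome (after 17 weeks) = outcome (baseline) + study group + covariates". The 9-month model is "MVPA (9-month post-intervention F/U) = MVPA (after 17 weeks) + study group + covariates", and the sentence introducing it says outright that 17-week MVPA is being controlled for. Baseline MVPA does not appear in it.

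Two general statements also bear on the point. Data analysis describes a multilevel approach "that will incorporate baseline measures as covariates", and Primary analyses says that effect sizes will be adjusted for baseline outcome values. The same section states "Primary analysis is of intention to treat type". Nowhere is a 9-month model given without the 17-week term.

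**The concern.** Baseline MVPA is fixed before allocation, so adjusting for it sharpens the comparison without changing what is compared. MVPA at 17 weeks is a result of allocation. Holding it constant compares intervention and control girls who had reached the same activity level at the end of the programme. That removes whatever part of the 9-month difference is carried forward from the 17-week gain, and carrying that gain forward is how a lasting effect would be expected to arise.

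The protocol's own mediation plan shows the logic. Under Secondary analyses, a 17-week variable is added to the outcome model to see how far the group effect shrinks. The 9-month model has the same structure but is listed as a primary analysis of effect.

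According to Study design, physical activity is the only thing measured at 9 months, so every statement about lasting benefit depends on this one model. The direction of the error is also perverse: for a given true 9-month benefit, the better the intervention worked at 17 weeks, the smaller the 9-month estimate.

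**Working it through.** **Inputs from the protocol article**
- 17-week difference D17 = 16 minutes/week (Aims and hypotheses). Power calculations gives the same figure: effect size 0.20 x SD 80 = 16.
- SD 80 minutes per 7 days, ICC 0.02, 12 schools per arm, 50 girls per school, two-sided alpha 0.05 (Power calculations).

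**Assumptions, because the protocol gives no figure**
- Equal SDs at all time points, so that the within-arm slope b of 9-month on 17-week MVPA equals the correlation r. Range 0.3 to 0.7.
- True 9-month difference D9 of 16 (fully sustained), 8 (half) or 4 (a quarter).

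**What the written coefficient estimates.** With parallel within-arm lines of slope b, the group coefficient is the vertical gap between them:

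coefficient = D9 - b x D17

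It equals D9 only if D17 = 0, which the protocol hypothesises against, or b = 0, which is implausible for repeated measurements of the same girls. It is zero when D9/D17 = b and negative when D9/D17 is below b.

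| True D9 | b = 0.3 | b = 0.5 | b = 0.7 |
|---|---|---|---|
| 16 | 16 - 4.8 = 11.2 | 16 - 8.0 = 8.0 | 16 - 11.2 = 4.8 |
| 8 | 3.2 | 0.0 | -3.2 |
| 4 | -0.8 | -4.0 | -7.2 |

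**Simulation check.** 600 simulated trials of 24 schools x 50 girls, with SD 80, ICC 0.02, D17 = 16 and equal correlation r between all three time points, gave these mean coefficients for r = 0.3, 0.5, 0.7:

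| Model for 9-month MVPA | True D9 = 16 | True D9 = 8 |
|---|---|---|
| As written (17-week term) | 11.5, 8.0, 4.7 | 3.3, 0.2, -3.1 |
| Baseline term instead | 16.2, 16.0, 15.7 | 7.9, 8.2, 8.1 |
| Both terms | 12.5, 10.6, 9.3 | 4.2, 2.9, 1.5 |

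**Both terms, by formula.** With equal correlations, the slope on 17-week MVPA given baseline is r/(1 + r), that is 0.231, 0.333 and 0.412. A true 16 becomes 12.3, 10.7 and 9.4. A true 4 becomes 0.3, -1.3 and -2.6.

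**Power for a fully sustained effect.** The protocol states none for 9 months. The design effect is 1 + 49 x 0.02 = 1.98, and the standard error is 80 x sqrt(1 - r^2) x sqrt(2 x 1.98/600). At r = 0.5 that is 80 x 0.866 x 0.0812 = 5.63. Baseline-adjusted power is then Phi(16/5.63 - 1.96) = 0.81. As written, it is 0.30, from Phi(8/5.63 - 1.96). For r = 0.3, 0.5 and 0.7, power is 0.73, 0.81 and 0.93 with baseline adjustment, against 0.44, 0.30 and 0.18 as written.

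These are normal approximations. The same method gives 0.69 for the unadjusted 17-week comparison, where the protocol states 0.80. That is a separate matter and the present point does not depend on it.

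**The case against.** The strongest reply has four parts.

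**The model may be deliberate.** The protocol's background worries about maintenance after an intervention ends, and a model conditional on 17-week MVPA addresses change from that point. That is a legitimate exploratory question, but it is not the stated hypothesis, which concerns which arm is more active at 9 months. Nor is it a clean answer to the maintenance question, because unmeasured causes shared by 17-week and 9-month activity affect the conditional comparison.

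**Baseline MVPA may enter as well.** The general statements about baseline adjustment allow the equation to be read as incomplete. This has some force: the attenuation is then milder, and a half-sustained effect stays positive across the range examined. But a true 16 is still estimated as about 12.3 to 9.4, and a true 4 is already negative at r = 0.5. Only removing the 17-week term cures the problem.

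**Some side points are weaker.** Losing girls without a valid 17-week record depends on how missing covariates are handled. Preliminary analyses assumes missing at random and leaves the method open. On intention to treat, the model keeps girls in their allocated group. What it gives up is the comparison of the groups as randomised, because it conditions on a later outcome. The conclusion needs neither point.

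**The primary outcome is untouched.** This is true: the 17-week model adjusts for baseline and is sound in this respect. The 9-month comparison is nevertheless part of the main aim and a listed hypothesis.

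**Conclusion.** The concern holds. The 9-month model as written estimates D9 - b x D17, not the difference between arms that the protocol hypothesises, and no other text supplies a model that does.

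That the target is wrong follows from the model itself. The size depends on two things. One is the protocol's own expected gain of 16 minutes/week at 17 weeks. The other is an assumed slope of 0.3 to 0.7, with equal SDs. Under these, the model takes 4.8 to 11.2 minutes/week off the 9-month effect. If baseline MVPA is also in the model, with equal correlations over the same range, it takes off about 3.7 to 6.6. A null or reversed estimate is not certain: without the baseline term, it arises when the share of the 17-week gain still present at 9 months is no larger than the slope.

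This must be corrected before the 9-month data are analysed. It does not affect the 17-week primary result.

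**What to change.** Replace the 9-month model with: 9-month MVPA = baseline MVPA + study group + prespecified covariates, with the same school random effect as the 17-week model.

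Alternatively, fit one longitudinal mixed model to 17-week and 9-month MVPA, adjusted for baseline, with a group-by-time term, and read the 9-month contrast from it. This also keeps girls who miss one of the two follow-ups, in line with the missing-at-random assumption already made.

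If change after the end of the intervention is of interest, keep the 17-week-adjusted model as a labelled exploratory analysis and say that its group coefficient is not the 9-month intervention effect.

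The cost is one line of the analysis section. Baseline MVPA is already collected, and no change to design, sample or measurement is needed.
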